## Methods and analysis

### Design

A pragmatic, single-arm, multisite, mixed-methods longitudinal study. The study design has been developed in line with the latest Medical Research Council (MRC) guidelines,^32 33^ which recommend an iterative intervention development and evaluation process. Mixed-methods, pragmatic study designs are recognised as an appropriate way for researchers to approach the development and evaluation of complex interventions in palliative care.^34^ We are employing a convergent design to integrate quantitative measures of fidelity, feasibility, acceptability and possible impact, with semi-structured interviews and focus groups. In the qualitative aspect of the study, we will take a phenomenological approach to capture more nuanced feedback on the participants’ experience of the intervention, including their views on its design, acceptability and any perceived effects.^34 35^ The quantitative and qualitative data will be integrated through a process evaluation. As the focus of the study is on applying pragmatic mixed-methods to optimise intervention design, this study will not formally evaluate nor test *a priori* hypotheses regarding its efficacy or report p-values.

The study is approved by the University College London Research Ethics Committee (reference: 15281/002).

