### Participants

The study will be conducted in three population groups recruited from participating hospices:

#### Group 1

Up to 40 adults living with terminal illness receiving palliative care from a UK hospice (on an inpatient, day care, outpatient or community basis). A sample size of 40 is recognised by the National Institute of Health Research as being appropriate for intervention feasibility and pilot work that is not designed to evaluate efficacy.^36 37^

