### Recruitment

#### Group 1

We will employ convenience sampling. This is a pragmatic decision based on difficulties recruiting participants during the COVID-19 pandemic; the target numbers for recruited participants are in place to manage the scope of the research. We will assess recruitment rate as part of the study’s feasibility assessment. The recruitment window has been selected based on research team capacity and funding availability.

Clinical and research staff at hospice sites will identify patients who may be eligible to participate between October 2020 and January 2021. They will make initial contact, explain the study and if the participant is interested, provide them with an invitation letter, email or link to the study website. The study website hosts the participant information sheet and a link to an online reply form. Participants can indicate on the reply form if they would or would not like to take part.

If participants select yes on the reply form, they can progress to the online informed consent and advance consent form, which asks what participants would like to happen to their data if they lose capacity over the course of their participation in the study. If they select no, they have the option to provide their reasons for not taking part. There is also an option to request further information from the research team before making a decision. If participants select this option, they are prompted to provide their contact details and a member of the research team will phone or email them to discuss the study further. If, having discussed the study, participants choose to take part, they can progress to the online informed consent and advance consent forms. The research team will inform the relevant hospice when a participant from their service consents to take part, so it can be recorded on their patient notes. The participant will be reminded of their right to withdraw from the study at any time throughout the study in online materials and through direct communication with the research team.

In the initial phase of the study, all Group 1 participants will be invited to take part in a semi-structured interview. Depending on uptake, once a third (n=5) have been recruited to interview phase, we will assess the mix of participants in terms of demographic characteristics, to inform recruitment targets according to a purposive sampling framework.

#### Group 2

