Feedback form	Immediately after final expression session	Participants will be asked to complete an online feedback form exploring their experience of completing the intervention, if they needed any assistance from a carer and the nature of that assistance, and their fidelity to the protocol. The feedback form questions were informed by work on ethical research in vulnerable populations^65^ and the theoretical framework of acceptability for healthcare system interventions.^53^	Quantitative and qualitative	Descriptive statistics and combined deductive and inductive thematic analysis	Feasibility and acceptability Impact on well-being Outcome measure selection Underlying mechanisms
Semi-structured interview	Within 8 weeks of final expression session	Exploring participants’ experience of the intervention and questionnaires, including whether they experienced any negative feelings during or after each expression, whether they found the intervention helpful and the appropriateness and relatability of the expression session prompts, expanding on the topics covered in the feedback form	Qualitative	Combined deductive and inductive thematic analysis	Feasibility and acceptability Impact on well-being Outcome measure selection Underlying mechanisms

*All measures will contribute to the primary objective: optimisation of the intervention as informed by a process evaluation (see table 3).

BIR, blinded independent review; LIO, let it out; LIWC, linguistic inquiry word count.

#### Expression sessions—group 1

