*The research team will have a dedicated study phone that a member of the research team keeps only on their person during working hours (09:00–17:00 Monday–Friday) and is kept in a secure locked cabinet outside of those hours. The phone will be checked once a day for recordings or photos received, at which point the recording will be transferred to the dedicated project file on Data Safe Haven and deleted from the phone.

#### Self-report measures—group 1

All self-report data is collected online using the Research Electronic Data Capture (REDCap) online survey platform.^47 48^ Group 1 participants will complete a demographics questionnaire at baseline (prior to receiving the intervention). They will also complete a series of health-related questionnaires at baseline and 1, 4 and 8 weeks after the final intervention session (secondary outcome measures). Group 1 participants will also be prompted to log in to the platform during or after each expression session to indicate they have completed the session, and (if they wish) to share their response with the research team. Directly after each expression session they will also be prompted to complete a short self-report questionnaire to monitor their mood, and perception of how meaningful and personal the session was (secondary outcome measures). After the final expression session, participants will also complete a feedback form (primary outcome measure).

#### Semi-structured individual interviews (primary outcome measure)—group 1

Semi-structured interviews (n≤15) will be conducted within 8 weeks of the participant’s final expression session. Interviews will be conducted by DM, following a topic guide to explore participants’ experience of the intervention and questionnaires, including whether they experienced any negative feelings during or after each expression, whether they found the intervention helpful and the appropriateness and relatability of the expression session prompts, expanding on the topics covered in the feedback form.

Interviews will take place virtually and will be audio-recorded using Microsoft Teams, to minimise face-to-face interactions in line with government COVID-19 guidance. Recordings will be transcribed verbatim for analysis; transcripts will be pseudonymised and personally identifiable information redacted from the transcript.

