#### Overview—group 2 and 3 (primary outcome measures)

Semi-structured interviews will also be conducted with ≤15 informal carers of Group 1 participants after they have completed their final expression session. Focus groups or semi-structured interviews (depending on practicalities of arranging a suitable time) with ≤30 hospice staff and volunteers will also be conducted. As with Group 1, interviews and focus groups will be conducted by DM, and will follow topic guides designed to explore participants’ views on the design and content of LIO; if and how it may need to be adapted; potential risks of harm or benefit; where LIO might fit into current pathways of care; and what help may be needed to support its implementation. All Group 2 and 3 participants will complete an online demographics questionnaire prior to taking part in the interview/focus group.

As with Group 1, interviews and focus groups will take place virtually and will be audio-recorded using Microsoft Teams. Recordings will be transcribed verbatim, pseudonymised and personally identifiable information redacted from the transcript for analysis.

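### The feedback form, the patient and carer interviews and the follow-ups are timed from the final expression session, with no trigger for people who stop early, so form-based acceptability may describe mainly completers

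*Protocol article*

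**What the plan says.** All references are to the protocol article.

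- **Feedback form.** Under Self-report measures for Group 1: "After the final expression session, participants will also complete a feedback form (primary outcome measure"). Table 1 gives its time point as "Immediately after final expression session".
- **Patient interviews.** "Semi-structured interviews (n≤15) will be conducted within 8 weeks of the participant’s final expression session". The Recruitment section invites all Group 1 participants in the initial phase. After five have been recruited to interview, "we will assess the mix of participants in terms of demographic characteristics, to inform recruitment targets according to a purposive sampling framework".
- **Carer interviews.** "Semi-structured interviews will also be conducted with ≤15 informal carers of Group 1 participants after they have completed their final expression session".
- **Health measures.** Table 1 places every post-baseline point (immediate, 1, 4 and 8 weeks) relative to the final expression.
- **Staff interviews and focus groups.** These are also a primary measure, and they have no session trigger.
- **Sources for acceptability.** The acceptability row of Table 3 lists the feedback form and the interviews and focus groups. The withdrawal questionnaire appears only in the coverage-and-reach row and the contextual-factors row.

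The article does not define the final session for someone who does fewer than three, and states no alternative date for that person.

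**The concern.** The primary objective is to optimise the design of LIO, and people who could not or would not finish are a main source on what to change. A secondary objective is to identify adverse effects. The interview asks about negative feelings during or after each session, yet someone who stops because of such feelings has no defined date for the form or the interview.

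If the form is issued only after session 3, its results condition on completion. Whatever drives people to stop, if it is related to how they find LIO, is then filtered out of a primary outcome. This cannot be repaired at analysis, because the missing feedback was never requested.

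**Working it through.** **1. Is there a figure to reproduce?** No. Group 1 is set by convention ("Up to 40 adults living with terminal illness receiving palliative care from a UK hospice"), and the Design section says that "this study will not formally evaluate nor test" hypotheses on efficacy. The article gives no expected completion rate, no expected acceptability and no acceptability threshold.

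**2. Can the trigger work for someone who stops early?** There are two readings of *final session*.
- *Session 3.* A person who stops after session 1 or 2 never reaches the trigger.
- *The last session that the person did.* The interview ("will be conducted within 8 weeks of the participant’s final expression session") could still be arranged, because the date can be fixed in retrospect. The form could not reliably be issued: it is due immediately, and at the end of session 1 nobody knows that no further session will follow. The immediate health measures have the same problem.

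On either reading, the form has no workable trigger for an early stopper.

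**3. What else reaches early stoppers?**

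| Source | Reaches stoppers? | Enters the feedback-form result? |
|---|---|---|
| Initial interview invitation to all of Group 1 | Yes, though the timing is tied to the final session | No |
| Ratings after each session | Yes, for sessions done; covers how personal and meaningful the session was, and mood | No |
| Researcher contact at end of weeks 1 and 2 | Yes; stated purpose is well-being | No |
| Withdrawal questionnaire | Presumably those who withdraw; used for reach and context | No |
| Completion and retention percentages | Counts them | No |
| Staff interviews and focus groups | Independent of patient completion | No |

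**4. How large could the effect be?** Let c be the proportion of starters who complete, p_c acceptability among completers and p_s acceptability among stoppers. Suppose only completers fill in the form.

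- All starters: p = c × p_c + (1 − c) × p_s
- Overstatement: p_c − p = (1 − c) × (p_c − p_s)

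Every rate below is an assumption, as is the yes/no reading of acceptability.

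*With p_c = 80% and p_s = 30%* (difference 50 points):

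| Non-completion (1 − c) | Overstatement | All starters |
|---|---|---|
| 10% | 0.1 × 50 = 5 points | 75% |
| 20% | 0.2 × 50 = 10 points | 70% |
| 30% | 0.3 × 50 = 15 points | 65% |
| 40% | 0.4 × 50 = 20 points | 60% |

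*With p_c = 90%, and completion from 90% down to 50%:*

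| p_s | Overstatement |
|---|---|
| 90% | 0 |
| 80% | 1 to 5 points |
| 40% | 5 to 25 points |
| 20% | 7 to 35 points |

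**5. Bounds without a guess at p_s.** Suppose 40 start, 80% complete (32 forms) and 29 of the 32 are positive (29/32 = 91%). Counting all 8 stoppers as negative gives 29/40 = 72.5%. Counting all 8 as positive gives (29 + 8)/40 = 37/40 = 92.5%. The form alone cannot place the all-starter figure more narrowly than this.

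**The case against.** The strongest case against has five parts.

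- **No passage excludes early stoppers.** This is right. A reader might infer a rule that people who stop supply no primary outcome. The article states no such rule: the interview invitation is open to all of Group 1, and interview timing can be read relative to a person's own last session. What stands is narrower: the article gives the form no trigger that works for a stopper.
- **Other data cover them.** Partly right. It would be wrong to say that fidelity and impact describe completers only. Fidelity includes the percentage completing all three sessions, and impact includes mood checks taken after each session. The contextual-factors row uses the withdrawal questionnaire and asks about barriers, which does serve optimisation. None of this supplies stoppers' answers to the acceptability items on the form.
- **The bias may be nil.** Correct. In this population some will stop through deterioration or death, not dislike. A reader might infer that acceptability *is* overstated; the documents support only *may be*. Nor does the positivity bias that the article acknowledges help here. That bias concerns the lead analyst's closeness to the intervention, which is a different mechanism.
- **An article condenses.** The full protocol may define what happens at discontinuation, and the existence of a withdrawal questionnaire suggests that some procedure exists. But the timing is not simply left out: Table 1 and the text both fix it, and Table 3 fixes the acceptability sources.
- **Nothing is tested.** There is no hypothesis test, p-value or acceptability threshold, so no formal decision turns on the figure. That limits the consequence but does not remove it, since the form feeds the primary objective directly.

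**Conclusion.** The point holds in a limited form. The feedback form, the patient and carer interviews and all post-baseline health measures are timed from the final expression session, with no stated trigger for people who stop after session 1 or 2. The acceptability row of Table 3 omits the withdrawal questionnaire. Staff interviews and focus groups are unaffected.

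Form-based acceptability may therefore reflect mainly completers and may be overstated. The article does not allow the amount to be derived. The figure of 5 to 20 points rests on assumed acceptability of 80% and 30% with 10% to 40% non-completion, and the amount is zero if stoppers and completers rate LIO alike. The conclusion also assumes that the full protocol, which is not shown, does not already supply a trigger for early stoppers.

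**What to change.** 1. **Form.** Offer it, as optional, to every participant who started LIO: at session 3, at discontinuation or at the end of the 2-week window, whichever comes first. Word the items so that they apply after fewer than three sessions. The researcher contact already planned at the end of week 2 can serve as the prompt.
2. **Follow-ups.** For early stoppers, time the 1-, 4- and 8-week measures from that same date.
3. **Table 3.** Add the withdrawal questionnaire to the acceptability sources.
4. **Interviews.** Add completion status to the purposive frame, so that some of the 15 or fewer patient interviews go to people who stopped.
5. **Reporting.** Give acceptability by number of sessions completed, with the number of starters as the denominator. Some stoppers will be too unwell to respond, so show the bounds from step 5 of the working for forms still missing.

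The cost is a changed survey trigger, some rewording of the form and a few sentences in the protocol, with no additional participants. The downsides are slight extra burden for seriously ill people who have already stopped, which is why the form should be optional, and possibly a less favourable acceptability figure.

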#### Overview—group 2 and 3 (primary outcome measures)

Semi-structured interviews will also be conducted with ≤15 informal carers of Group 1 participants after they have completed their final expression session. Focus groups or semi-structured interviews (depending on practicalities of arranging a suitable time) with ≤30 hospice staff and volunteers will also be conducted. As with Group 1, interviews and focus groups will be conducted by DM, and will follow topic guides designed to explore participants’ views on the design and content of LIO; if and how it may need to be adapted; potential risks of harm or benefit; where LIO might fit into current pathways of care; and what help may be needed to support its implementation. All Group 2 and 3 participants will complete an online demographics questionnaire prior to taking part in the interview/focus group.

As with Group 1, interviews and focus groups will take place virtually and will be audio-recorded using Microsoft Teams. Recordings will be transcribed verbatim, pseudonymised and personally identifiable information redacted from the transcript for analysis.

### Data analysis

#### Primary objective: process evaluation and intervention proposal

Using the qualitative and quantitative data collected from Groups 1, 2 and 3 (and in combination with evidence that has informed this research protocol from prior work (reviews and a trial) conducted by the research team), a triangulation approach will be applied drawing on process evaluation methodology.^35^ Process evaluation is recognised as a valuable, pragmatic method to optimise intervention design and inform evaluation during feasibility testing phases.^35^ Through the process evaluation, we aim to develop a preliminary theoretical model to inform understanding of potential causal mechanisms of LIO and any contextual and implementation factors that may be associated with any potential variation in outcomes. Insights from the process evaluation will inform the final intervention proposal. Table 3 describes the framework that will be used to guide the integration of mixed-methods data for the process evaluation. We developed the framework based on the MRC guidance on conducting process evaluations.^35^

**Table 3 T3:** Framework guiding analysis and integration of mixed-methods data for process evaluation

	Research questions	Data source	Data analysis
Implementation	Coverage and reach (retention): What percentage of Group 1 participants completed the intervention? What are the demographics of participants who took part in the study and completed the intervention? What were the reasons given for non-participation?	Recruitment/data collection records Demographics questionnaire Researcher reflective notes and informal feedback from research sites; withdrawal questionnaire	Descriptive statistics Inductive thematic analysis
	Fidelity, frequency and duration (adherence): To what extent was the intervention implemented as planned? What percentage of participants completed all three expression sessions, within the 20–30 min time frame, in a private space? What percentage of expression sessions were assigned to the correct prompt by a blinded assessor? To what extent do expression session transcripts use emotion and positive emotion words?	Recruitment/data collection records Group 1 feedback form Interviews and focus groups with Group 1, 2 and 3 Expression session texts	Descriptive statistics Blinded assessor review LIWC analysis
	Acceptability: How acceptable is the intervention for people living with terminal illness receiving care from hospices, their informal carers and hospice staff? What factors affect its acceptability?	Group 1 feedback form Interviews and focus groups with Group 1, 2 and 3	Descriptive analysis and inductive thematic analysis coded to concepts in the TFA
Impact and mechanisms	Impact: What are the perceived benefits of the intervention from the perspective of people living with terminal illness, their informal carers and hospice staff? Are there any changes in scores of psychological and physical health measures before and after (immediately, 1, 4 and 8 weeks post intervention)?	Group 1 feedback form Interviews and focus groups with Group 1, 2 and 3 Physical and psychological health-related outcome measures and mood checks	Inductive thematic analysis Descriptive pre–post statistics
	Mechanisms of impact: What cognitive processes are taking place during each expression session? Are there any patterns in the characteristics of participants who perceive benefits?	Expression session texts Demographic questionnaires	LIWC Descriptive statistics
Contextual factors	What factors at political, economic, organisational and individual level affected, or might be expected to affect, the implementation and/or impact? What options are there to minimise any barriers to successful implementation?	Group 1 feedback form Interviews and focus groups with Group 1, 2 and 3 Researcher reflective notes and informal feedback from research sites; withdrawal questionnaire	Inductive thematic analysis

LIWC, linguistic inquiry word count; TFA, the theoretical framework of acceptability.

Analysis will be led by DM in iterative consultation with the research team and advisory group. Codes, themes, descriptive statistics, data integration and conclusions generated by DM will be checked at key stages throughout the project by the research team. This will help minimise any risk of a positivity bias arising from DM’s close connection to the intervention being developed, and help validate the integrity of DM’s interpretation of the data. Thematic analysis will be carried out using QSR International NVivo V.11.4 software.^49^ Quantitative responses will be summarised using SPSS V.24.^50^

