### Data collection

#### Overview—group 1

Table 1 provides a detailed description of the participant timeline and outcome measures for Group 1 participants.

**Table 1 T1:** Group 1 participant timeline, outcome measures and analysis approach

Measure	Time points administered	Description	Data type	Analysis approach	Relevant research objective*
Demographics	Baseline	Approximate date of hospice referral, age, gender, ethnicity, marital status, religious background, level of education, type of care (eg, inpatient, outpatient, day care), diagnosis, mental health history and COVID-19 status.	Quantitative	Descriptive statistics	1. Feasibility and acceptability
Expression sessions	Three sessions over 2-week intervention period	Typed, handwritten or audio-recorded responses to three expression sessions that make up the LIO intervention.	Quantitative and qualitative	LIWC and BIR inductive thematic analysis (session 2)	Feasibility and acceptability Underlying mechanisms Exploratory objective (session 2)
Health-related outcome measures (see below for details)	Baseline, immediately after the final expression, and, 1 week, 4 weeks and 8 weeks after the final expression	See below for details.	Quantitative	Descriptive statistics and descriptive pre–post analysis	Feasibility and acceptability Impact on well-being Outcome measure selection Underlying mechanisms
Integrated Palliative Care Outcome Scale (IPOS)—patient version^56^		An updated, brief (10 questions, 17 items) version of the POS instrument. IPOS was developed specifically to capture a range of the most important concerns of people living with palliative-stage disease, covering symptoms, information needs, practical concerns, anxiety or low mood, family anxieties and overall feeling of being at peace. Items in question 2–9 are scored from 0 to 4, and overall scores can range from 0 to 68. Questions 1 and 10 are not scored.			
Patient Health Questionnaire 9^57^		A 9-item instrument developed to screen for major depressive disorder, and validated in palliative care populations.^58^ Items are scored 0 to 3, and it can be scored continuously or with validated cut-offs for mild (5 to 9), moderate (10 to 14), moderately severe (15 to 19) and severe depression (20 to 27).^59 60^ The cut-off for a depression ‘case’ is 10.			

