##### Impact on psychological and physical well-being

Inductive thematic analysis of interviews and feedback from free-text responses from patients, carer and staff participants. DM will develop codes from the raw data, to be checked and adjusted by the research team; data will be re-coded, checked and adjusted until code saturation is reached.Descriptive pre–post analysis of changes in outcome measures (Integrated Palliative Care Outcome Scale, Patient Health Questionnaire 9, Generalised Anxiety Disorder 7, Sleep Quality Scale, uptake on mental health services): mean and standard deviation of scores at each time point.Descriptive summary of number of adverse effects reported by clinical team and participants.

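### The impact question asks about change in scores, but the stated summary (mean and SD at each time point) does not show how precisely any within-person change is estimated

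*Protocol article*

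**What the plan says.** In the protocol article, the Impact row of Table 3 (Data analysis, primary objective) asks: "Are there any changes in scores of psychological and physical health measures before and after (immediately, 1, 4 and 8 weeks post intervention". It assigns descriptive pre–post statistics to that question.

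The section on impact on psychological and physical well-being lists what is analysed ("Integrated Palliative Care Outcome Scale, Patient Health Questionnaire 9, Generalised Anxiety Disorder 7, Sleep Quality Scale, uptake on mental health services") and defines the summary as "mean and standard deviation of scores at each time point". Four of these are numeric scores. The fifth is a form answered yes, no or prefer not to say.

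Table 1 gives the measurement times as "Baseline, immediately after the final expression, and, 1 week, 4 weeks and 8 weeks after the final expression". The text on Group 1 self-report measures says participants "complete a series of health-related questionnaires at baseline and 1, 4 and 8 weeks after the final intervention session", which leaves out the measurement immediately after the final session.

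The Design section says that "this study will not formally evaluate nor test" a priori "hypotheses regarding its efficacy or report p-values". The number of patients is capped at 40, supported by a citation: "A sample size of 40 is recognised by the National Institute of Health Research as being appropriate for intervention feasibility and pilot work".

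The pre–post results are then used. The section on choice of outcome measure draws on them, together with the qualitative material, to infer which measures may suit a later evaluation. The section on underlying mechanisms triangulates indicators of impact with the word-count analysis to develop a preliminary theoretical model.

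**The concern.** The question is about change, while the named summary describes levels. With complete follow-up, the difference between two means equals the mean change, but nothing shows how variable that change is between people or how precisely its mean is estimated. With incomplete follow-up, the two means also come from different sets of people, so even the size of the mean within-person change is not shown.

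This matters because the numbers inform later choices. Someone choosing among four instruments will naturally look at which one moved. With 40 people or fewer, an instrument can appear to move through random error alone, and a table of means and SDs gives no way to tell. The same applies to impact indicators that enter the theoretical model. The team's checking of the lead analyst's conclusions, which the protocol offers as protection against positivity bias, would rest on the same table.

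**Working it through.** **The plan's own figure.** The only design number is the cap of 40. It rests on a citation, with no effect size, SD, alpha or power, so there is no calculation to reproduce.

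**Inputs from the document.** n ≤ 40; four scored measures (IPOS, PHQ-9, GAD-7, sleep); four follow-ups by Tables 1 and 3, or three by the self-report text. That gives 4 × 4 = 16 or 4 × 3 = 12 comparisons with baseline.

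**Assumptions not in the document.** No true change; equal SD at each time; complete data; between-time correlation r of 0.5–0.7; between-measure correlation of 0.4–0.6; n = 25 as an illustration of fewer completers.

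**Step 1: what the marginal SDs leave out.** With equal SDs, the SD of the paired change is SD × √(2(1 − r)). The 95% half-width of the mean change, in SD units, is t(0.975, n − 1) × √(2(1 − r)/n).

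| n | r | calculation | half-width (SD) |
|---|---|---|---|
| 40 | 0.3 | 2.023 × √(1.4/40) | 0.38 |
| 40 | 0.5 | 2.023 × √(1.0/40) | 0.32 |
| 40 | 0.7 | 2.023 × √(0.6/40) | 0.25 |
| 40 | 0.8 | 2.023 × √(0.4/40) | 0.20 |
| 25 | 0.5 | 2.064 × √(1.0/25) | 0.41 |
| 25 | 0.7 | 2.064 × √(0.6/25) | 0.32 |

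At n = 40, the same printed means and SDs are compatible with a half-width anywhere from 0.20 to 0.38 SD, depending on a correlation that the reader is not given.

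**Step 2: chance differences, one comparison.** At n = 40 the standard error of a mean change is √(1.0/40) = 0.158 SD at r = 0.5 and √(0.6/40) = 0.122 SD at r = 0.7. A favourable difference of at least 0.2 SD then lies 1.26 or 1.63 standard errors from zero. With no true change it occurs in about 10% or 5% of studies.

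**Step 3: at least one of the comparisons.** Vectors of means were simulated under no change with exchangeable correlations (the cross-measure, cross-time correlation is the product of the two). The largest favourable difference from baseline was counted. For n = 40, 16 comparisons and a threshold of 0.2 SD:

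| r (between times) | between measures | at least one ≥ 0.2 SD, favourable |
|---|---|---|
| 0.5 | 0.4 | 59% |
| 0.5 | 0.6 | 53% |
| 0.7 | 0.4 | 39% |
| 0.7 | 0.6 | 34% |

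Separate simulation runs put the lower end at 33% or 34%, hence roughly 33–59%. With 12 comparisons the range is 29–53%, so the mismatch between Table 1 and the text does not alter the conclusion. At n = 25 with 16 comparisons it is 51–73%.

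**The case against.** The strongest reply is that the study never claims to detect an effect. It is single arm, says that it is not designed to evaluate efficacy, and excludes hypothesis tests and p-values. The scores are secondary, are triangulated with interviews, focus groups and feedback forms, and feed a model described as preliminary. Table 3 poses guiding questions and contains no decision rule. A condensed article may also leave the layout of tables to a fuller document.

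Most of this stands, and it limits the point. A reader might infer that the analysis declares change almost every time. Under the same assumptions, at least one mean improves by some non-zero amount in 96–98% of studies with no effect. But nothing in the protocol turns a non-zero difference into a finding, so that is not an operating characteristic of the plan. A reader might also infer that the scores alone carry the evidence of impact, and the triangulation contradicts that.

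Two parts of the reply do not dispose of the point. Excluding p-values does not exclude confidence intervals. And this is not only a matter of condensed detail: the article states which summary will answer the question about change, and that summary does not show the precision of change.

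**Conclusion.** The point holds as a mismatch between question and summary, with a cheap remedy. At the planned maximum of 40, a mean change would carry a 95% half-width of about 0.25–0.32 SD (r = 0.7 to 0.5), and the stated summary does not let a reader see this. In roughly 33–59% of studies with no true change, at least one favourable difference of 0.2 SD or more would appear. That range depends on the assumed correlations, complete data and the chosen 0.2 SD threshold, none of which comes from the protocol. It describes a risk of over-reading when outcome measures are chosen and the preliminary model is built. It is not a false-positive rate of a planned test, and it leaves the primary objective of design optimisation intact.

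**What to change.** In the section on impact on psychological and physical well-being, and in the Impact row of Table 3, report for each scored measure and follow-up: the number of pairs, the mean paired change from baseline, the SD of change and its 95% confidence interval, without p-values. Reword the Table 3 question along the lines of *how large are the changes, and how precisely are they estimated*. State that the intervals are read jointly and reflect random error only; in a single arm they do not separate an effect from a time trend or from selective dropout.

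Do not use exclusion of zero to decide what enters the process evaluation. That would be an unadjusted 5% significance test, which the Design section rules out. With no true change, at least one of 16 intervals would still exclude zero in about 40–47% of studies. A true change of 0.2 SD would pass on a single comparison at n = 40 only 24–36% of the time.

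Two small items can be settled in the same edit. Reconcile Table 1 with the self-report text on the measurement immediately after the final session, and summarise the service-uptake items as counts, since a mean and SD do not suit them.

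The cost is a few extra table columns and a sentence or two of wording, with no new data. The downside is that some apparent changes will be shown to be imprecise. The SD of change is also a useful input for planning a later evaluation.
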